## Abstract

**Background:**

Government of India launched Anemia Mukt Bharat (AMB) program in 2018. Despite its implementation, the prevalence of anemia remains high. To address the gaps in coverage, adherence and effective implementation, the Indian Council of Medical Research (ICMR) initiated the **Pr**ecision driven **R**esponse for **A**nemia **C**ontrol **a**nd **S**ustainable **H**ealth (PRAKASH) study. It is an implementation research study aimed at co-developing and optimizing a district-level model of evidence-based anemia control interventions. The intended goal is to reduce anemia prevalence to 20% or lower through scalable, context-specific, and sustainable strategies.

**Methods:**

This multi-site study targets six key population groups: children (aged 6–59 months and 5–9 years), adolescents boys and girls (10–19 years), women of reproductive age (20–49 years) and pregnant women. Interventions are anchored in six pillar i. Test–Treat-Track until resolution, ii. prophylactic iron and folic acid supplementation, ensuring high complianceiii. anemia-relevant health interventions, iv. fortified rice distribution, v. dietary diversification and promotion of iron-rich foods, and vi. behavior change communication through Jan Andolan. Anemia prevalence will be estimated through a series of community-based cross-sectional surveys. Mixed methods approach will be employed to assess barriers and enablers at the individual, household, facility, and community levels. The study will utilize implementation science frameworks, including Consolidated Framework for Implementation Research (CFIR) and Expert Recommendations for Implementing Change (ERIC), to guide iterative implementation, real-time model refinement, and monitoring of performance. Information on outcome indicators will be collected to evaluate anemia prevalence, fidelity, feasibility, and service delivery improvements.

**Conclusion:**

The study will try to readdress the implementation challenges across diverse regions and aims to develop a comprehensive and replicable model for the AMB 2.0 program. The study is likely to contribute to the global evidence base on implementation science for anemia reduction in low- and middle-income countries.

## Introduction

Anemia is characterized by low number of red blood cells count or the haemoglobin concentration within them is lower than normal, which impairs the adequate oxygen supply to the tissues and organs [1]. The causes of anemia are multi-faceted comprising of genetic factors, dietary intake, nutritional deficiencies, chronic illnesses, inflammation, infections socio-economic conditions etc. [2–5]. Gender disparity and geographical settings also play significant role in its causation [6,7]. Anemia has several adverse health consequences including impaired cognitive development and stunting in children [8,9], reduced work productivity [10,11], and adverse pregnancy outcomes like stillbirths, preterm birth, low-birth-weight babies, and small for gestational age babies [12–14].

Anemia is a significant public health concern worldwide. According to the World Health Organization’s global anemia estimates, 2025, achieving the 2030 global nutrition target for anemia particularly among women of reproductive age will necessitate accelerated and innovative efforts [15]. India, with its substantial and diverse population, bears one of the highest burdens of anemia globally [16–19]. National surveys such as National Family Health Survey (NFHS)-2–5 have consistently highlighted the high prevalence of anemia, especially among pregnant women, adolescent girls, and young children [20–23]. Despite sustained efforts through programs such as the National Nutritional Anemia Prophylaxis Program and its subsequent expansions, the recent NFHS-5 estimate indicates that 57% of women of reproductive age, 52% of pregnant women, and 67% of under-5 children remain anemic [24]. These data underscore the importance of both the magnitude of the challenge and the opportunity to enhance and accelerate anemia control strategies through evidence-based, innovative, and locally tailored implementation models.

The Government of India launched the Anemia Mukt Bharat (AMB) program in 2018 with a target of reducing anemia prevalence by three percentage points per year across six beneficiary groups: children aged 6–59 months, children 5–9 years, adolescents 10–19 years, women of reproductive age (20–49 years), pregnant women, and lactating women. However, the program faced challenges with implementation variability across states due to limited awareness, side effects affecting compliance, lack of IEC materials, supply chain and logistic gaps, dietary diversity constraints, cultural barriers, behavioural and social factors and the COVID 19 pandemic. To consolidate the scientific foundation of these efforts, on the directives of National Institution for Transforming India (NITI) Aayog, the Indian Council of Medical of Research (ICMR) conducted a comprehensive evidence synthesis and stakeholder consultation exercise. This process reviewed global and national experience, identified best practices, and informed the development of a strengthened package of evidence-based interventions. These recommendations formed the basis of the proposed AMB 2.0, which has been submitted by NITI Aayog to the Ministry of Health and Family Welfare (MoHFW) for consideration. The six interventions—i. Test–Treat-Track until resolution, ii. prophylactic iron and folic acid supplementation, ensuring high complianceiii. anemia-relevant health interventions, iv. fortified rice distribution, v. dietary diversification and promotion of iron-rich foods, and vi. behavior change communication through Jan Andolan. [25–35].

The Precision driven Response for Anemia Control and Sustainable Health (PRAKASH) study has been designed to operationalize and test this evidence-based package through a precision-driven, multi-site implementation research study.The study utilizes a theory of change framework that posits for a precision-driven, district-level model that systematically identifies contextual bottlenecks and co-develops tailored implementation strategies (using CFIR determinants linked to ERIC strategies) that are context-specific, scalable, and sustainable with the aim to improve fidelity, reach, and continuity of the six AMB 2.0 pillars. Importantly, it seeks to address well-recognized programmatic challenges including variable Iron Folic Acid (IFA) coverage and adherence, supply chain bottlenecks, limited access to reliable diagnostic tools, and insufficient integration of strategies to tackle non-nutritional causes of anemia through an implementation science approach. By setting a goal of reducing anemia prevalence to below 20%, PRAKASH study aspires to provide a replicable framework that strengthens anemia control efforts and informs national scale-up.

Through this implementation study we aim to co-develop district model of Anemia Mukt Bharat 2.0 which would be optimized to increase coverage and adherence to reduce anemia prevalence to 20% or lower in beneficiary populations (children 6–59 months, adolescent girls (10–19 years), women of reproductive age (20–49 years), pregnant women). The primary objective would be to co-design, optimize, implement and evaluate a model of implementation strategies to deliver the AMB 2.0 interventions across target beneficiaries and reduce prevalence of anemia to ≤20%. The secondary objectives would focus to achieve high and effective population-based coverage (≥80%) of the AMB 2.0 interventions among target beneficiary groups and document the iterative process and implementation outcomes, in developing the optimized model.

## Methodology

### Study design and setting

The implementation research study will employ a mixed method approach (qualitative and quantitative) for model optimization and interrupted time-series measurements for the outcome evaluation. The six beneficiary groups currently under AMB program: i. Children (6–59 months), ii. Children (5–9 years) iii. Adolescent girls (10–19 years), iv. Adolescent boys (10–19 years) v. women of reproductive age (20–49 years), vi. pregnant women will be included in the study.

Formative research will be undertaken at the individual, community and facility level to identify barriers and facilitators for anemia management implementation across the six selected districts (Table 1). A series of total five cross sectional surveys (consisting of 2 baseline survey, an early implementation, mid implementation and an end-line survey) will be conducted to understand the factors affecting the implementation of the AMB 2.0 program at the individual, facility and community levels and the effectiveness of the implementation program. A thorough evaluation of the healthcare facilities and associated health care workers in the district will also be done to identify gaps that need to be addressed for effective implementation.

**Table 1 pone.0351414.t001:** Details of the study districts.

Sites	Anemia Prevalence as per NFHS-5	Geographical Area (Rural to Urban Ratio)
Site 1 Palghar, Maharashtra	Children 6–59 months: 70.3% Women 15–19 years: 52.1% Non pregnant women 15–49 years: 57.2% Pregnant women 15–49 yrs: 48.5%	52%:48%
Site 2 Koppal, Karnataka	Children 6–59 months: 68.1% Women 15–19 years: 45.6% Non pregnant women 15–49 years: 45.7% Pregnant women 15–49 yrs: 43.3%	79%:21%
Site 3 Palwal, Haryana	Children 6–59 months: 71.6% Women 15–19 years: 59.7% Non pregnant women 15–49 years: 57.2% Pregnant women 15–49 yrs: 56.8%	77%:23%
Site 4 Kendujhar, Odisha	Children 6–59 months: 46.6% Women 15–19 years: 68.2% Non pregnant women 15–49 years: 69% Pregnant women 15–49 yrs: 74.7%	86%:14%
Site 5 Sehore, Madhya Pradesh	Children 6–59 months: 82.4% Women 15–19 years: 50.5% Non pregnant women 15–49 years: 44.8% Pregnant women 15–49 yrs: 58.8%	81%:19%
Site 6 Medchal Malkajgiri District., Telangana	Children 6–59 months: 73.8% Women 15–19 years: 56.1% Non pregnant women 15–49 years: 57.4% Pregnant women 15–49 yrs:53.2%	9%:91%

During the implementation phase of the study, the initial model will be co-developed with key stakeholders, drawing on formative research findings and baseline survey results. Model will be refined through iterative, concurrent cycles of implementation, performance monitoring, incorporating stakeholder feedback. At each cycle, emerging barriers and facilitators will be analyzed using implementation science constructs to guide adaptations, thereby progressively optimizing the delivery model. The optimized model with potential to achieve high and effective coverage and impact, will be embedded and expanded across all blocks of the district, with the study team providing structured implementation support to government counterparts to ensure leadership engagement, capacity strengthening, and health system readiness. A predefined set of impact, implementation, and process indicators (as detailed in the later sections) will be monitored. Continuous learning from these indicators, including changes in anemia prevalence, improvements in service coverage, and fidelity to intervention delivery, will generate actionable insights that directly inform refinement of intervention strategies and outreach approaches, enabling adaptive, context-responsive scaling while preserving implementation quality.

### Study sites and participating institutes

The study sites and participating institutes for the PRAKASH study were selected through a transparent and competitive process coordinated by the Division of Reproductive and Child Health Nutrition at ICMR, New Delhi. An Expression of Interest for a “Multistate Implementation Research Study for the Development of a Sustainable, Scalable Model of Implementation Strategies for Prevention and Treatment of Anemia” was published on the ICMR website. A total of 102 proposals were received in response to the call. A screening committee, evaluated proposals based on predefined criteria including study design rigor, prior implementation research experience of the Principal Investigator, engagement with state and district health systems, collaboration with other stakeholders, and potential for integration with national programs. Following this process, six proposals were shortlisted, covering six sites across diverse geographic and socio-cultural settings in India. The participating institutes include ICMR-National Institute For Research in Reproductive and Child Health, Mumbai (Palghar, Maharashtra); St John’s Research Institute, Bangalore (Koppal, Karnataka); Society for Applied Studies, New Delhi (Palwal, Haryana); Kalinga Institute of Industrial Technology, Deemed University, Bhubaneswar and its affiliate institutions – Tata Institute of Social Sciences, Mumbai and InOrder-The Health Systems Institute, Hyderabad (Kendujhar, Odisha);All India Institute Of Medical Sciences Bhopal (Sehore, Madhya Pradesh); and ICMR-National Institute of Nutrition Hyderabad (Medchal Malkajgiri, Telangana). These sites were selected to represent diverse implementation environments and to collaboratively contribute to the development and optimization of a scalable anemia control model.

### Sampling strategy

For sampling purpose, the universe of study would be the entire district. For every cross-sectional survey, four blocks will be covered from the total number of administrative blocks within the district. Village/ward will be the primary sampling unit. Multi stage cluster sampling will be employed. In each selected village/ward, line list of beneficiaries (children, pregnant women, unmarried WRA (where available) and adolescents’ girls) will be collected from ASHA/ANMs/AWWs. It is recognized that the line listing will not have 100% coverage, but as a part of implementation research study, this aspect will be strengthened as interventions are rolled out. Beneficiaries will be selected randomly from the list. For the remaining groups, where ready line listing may not be available, the next 1–2 households where beneficiary was found using line listing, will be used to identify the rest of the beneficiary groups (children 5–9 years; adolescent boys; WRA & adolescent girls (incase CHWs do not have readily available list for WRA) in the stated order of priority. The sample will include a total of 50 beneficiaries from each village/ ward. The method of sampling would be the same in each of the five survey rounds.

**Sample size calculation:** It is assumed that the prevalence of anemia at baseline will be between 40–60% among different age groups as per NFHS-5 & Comprehensive National Nutrition Survey data. Assuming 20% prevalence of anemia at the end-line with 30% relative precision, 95% confidence interval, 1.45 design effect and assuming different non-response rate (40% for children 6–59 months and 5–9 years, 30% for adolescent girls and boys, 20% for women of reproductive age and 20% for pregnant women), the final sample size is calculated as 400 each for children 6–59 months and children 5–9 years, 350 each for adolescent girls and boys, 300 each for women for reproductive age group and pregnant women for each survey rounds. The focus of the study is on all the 6 groups; however, the four groups (children 6–59 months, adolescent girls (10–19 years), women of reproductive age (20–49 years), pregnant women) are selected for the evaluation of impact indicators. For the remaining two groups (children 5–9 y and adolescent boys), the focus is on the process and coverage indicators.

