**1. Impact level Indicator:**
**Primary outcome** will include prevalence of anemia among children 6–59months, adolescent girls (10–19yrs), and women of reproductive age and pregnant women (all trimesters)**Secondary outcomes** would include [1] prevalence of moderate anemia among children 6–59 months, adolescent girls (10–19 yrs), women of reproductive age and pregnant women (all trimesters); [2] prevalence of severe anemia among children 6–59 months, adolescent girls (10–19 yrs), women of reproductive age and pregnant women (all trimesters)

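### The only line list named for women of reproductive age covers unmarried women, so the marital mix of this primary-outcome sample depends on list availability and may drift between rounds

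*Protocol article*

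**What the plan says.** All references are to the protocol article.

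- **Target group.** Study design and setting lists the beneficiary groups, among them "v. women of reproductive age (20–49 years), vi. pregnant women will be included in the study". The Introduction and the sample size paragraph give the same 20–49 age band, also without regard to marriage. The sampling universe is the whole district.
- **Primary outcome.** The impact-level indicator is anemia prevalence in children 6–59 months, "adolescent girls (10–19yrs), and women of reproductive age and pregnant women (all trimesters").
- **List frame.** Under Sampling strategy, frontline workers in each village or ward supply a "line list of beneficiaries (children, pregnant women, unmarried WRA (where available"), with adolescent girls also listed. Then: "Beneficiaries will be selected randomly from the list".
- **Household step.** For groups without a ready list, "the next 1–2 households where beneficiary was found using line listing, will be used to identify the rest of the beneficiary groups". The groups reached this way include "WRA & adolescent girls (incase CHWs do not have readily available list for WRA) in the stated order of priority". No marital restriction is attached to this step.
- **Lists over time.** The same section concedes that line listing is incomplete and expects it to be strengthened as interventions roll out. Item 2 of the intervention package makes upkeep of beneficiary lists a task of the frontline workers. The sampling method is to be identical in all five rounds.

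**The concern.** The frame and the target population do not match. Married women who are not pregnant belong to the group defined as women aged 20–49 years, but the only WRA list named leaves them out. Making that list complete would not help, because a full list of unmarried women is still a list of a different population.

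The household step can bring married women in, but its use for WRA depends on whether a WRA list is available. The WRA sample is therefore a mixture of two sources, and the weights depend on a feature of the local health system that the intervention sets out to change. If unmarried and married women differ in anemia prevalence or in contact with the programme, two results are exposed:

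- the WRA prevalence in any one round, which is compared with the 20% target;
- the change between baseline and later rounds, on which the interrupted time-series evaluation rests. Keeping the written method constant does not keep the composition constant.

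WRA coverage indicators taken from the same interviews would be affected in the same way.

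**Working it through.** **1. The plan's own margin and sample size.** Inputs from the sample size paragraph: prevalence p = 0.20, relative precision 30%, 95% confidence, design effect 1.45, WRA non-response 20%, stated WRA size 300 per round.

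- Absolute margin: d = 0.30 × 0.20 = 0.06, or ±6 points.
- n = 1.96² × 0.20 × 0.80 / 0.06² = 170.7; times 1.45 = 247.6.
- Non-response: 247.6 / 0.80 = 309.5, or 247.6 × 1.20 = 297.1. The stated 300 lies between the two.
- With 300 approached and 20% non-response, 240 respond. Relative precision is then 30.5%, essentially as planned.

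Sample size is not the problem, and a larger sample would not reduce a frame error.

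**2. A formula for the composition effect.** Let f be the share of WRA interviews that come from villages using the list, u the unmarried share among women 20–49, s the unmarried share among WRA interviewed in list villages, and Δ the prevalence difference (unmarried minus married). Assume that the household step in the other villages reproduces the true mix u. Then

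- unmarried share of the sample = f·s + (1 − f)·u
- distortion of prevalence = f·(s − u)·Δ

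The literal reading is s = 1, giving f·(1 − u)·Δ. On the looser reading s is somewhere below 1 and is not fixed by the text. The distortion is zero only if s happens to equal u.

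**3. Illustration.** The documents give none of f, u, s or Δ. All values below are assumptions.

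Literal reading (s = 1), u = 0.15:

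| f | Unmarried share of sample | Δ = 2 | Δ = 5 | Δ = 10 |
|---|---|---|---|---|
| 0.50 | 0.50 + 0.50 × 0.15 = 57.5% | 0.9 | 2.1 | 4.3 |
| 0.75 | 0.75 + 0.25 × 0.15 = 78.8% | 1.3 | 3.2 | 6.4 |

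Entries are in percentage points; for example 0.50 × 0.85 × 10 = 4.25. With f = 0.50 and Δ = 10, moving u from 0.10 to 0.25 changes the result only from 4.5 to 3.8 points.

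Looser reading, for example s = 0.5 with f = 0.50 and u = 0.15: 0.50 × 0.35 × Δ = 0.175 × Δ, or about 0.4 to 1.8 points for Δ = 2 to 10.

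**4. Drift between rounds.** If f rose from 0.3 to 0.8 on the literal reading, composition alone would move apparent prevalence by 0.5 × 0.85 × Δ = 0.425 × Δ, again about 0.9 to 4.3 points for Δ = 2 to 10.

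**5. What the article offers on Δ.** Table 1 has only an age contrast: women 15–19 against non-pregnant women 15–49. The differences by site are −5.1, −0.1, +2.5, −0.8, +5.7 and −1.3 points (mean +0.15, median absolute difference 1.9). This is a poor stand-in for marriage, since the age bands overlap and 15–19 lies outside the WRA group. It shows no consistent direction and gives no reason to treat 5–10 points as typical, so the range used here starts at 2.

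**The case against.** A reader might infer that married non-pregnant women have no route into the sample wherever a list exists, and that the WRA estimate is therefore biased by several points. The text does not support that. The list is described as one of unmarried WRA, whereas the household step is triggered "incase CHWs do not have readily available list for WRA", without the word unmarried. A list of unmarried women is arguably not a list for WRA, so a village holding only that list would still send the team to households, where married women can be found. The adjective may also be a drafting slip. No rule says that a list, where present, fills the whole WRA allocation, and a journal article may leave that allocation to a field manual that is not shown.

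Further points stand. The size depends wholly on assumed inputs, and the direction is unknown. The article says that line listing in general will improve, not that unmarried-only lists will spread. Better lists could cover all WRA and shrink the problem. The household route should not be described as reaching only neighbours of young families, because adolescent girls are also listed and can serve as anchors. The survey tools are not shown, so marital status may already be recorded.

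These arguments defeat the strong version. They do not remove the dependence on list availability: on the looser reading the married and unmarried shares are still set by which lists exist and by an unstated split between list and household. Six sites working from the same sentence could sample this group differently.

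**Conclusion.** The concern holds in a limited form. The stated frame for WRA does not match the stated population, and on either reading the marital mix of the sample depends on list availability, which may change during rollout. The WRA prevalence estimate and its pre–post change can be distorted as a result, and the article states no fixed allocation or weighting that would prevent this.

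How large the distortion is, and in which direction, cannot be derived from the documents. About 1–4 points is an illustration that assumes the literal reading, half of WRA interviews from list villages, 15% of women unmarried and a prevalence gap of 2–10 points. The looser reading gives less. The planned margin for a single round is ±6 points. The correction should be made because the rule is fixed in the text and cheap to repair, not because a given bias has been shown.

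**What to change.** In Sampling strategy, define the WRA frame as all non-pregnant women aged 20–49 years regardless of marital status. Select them by one method in every village and every round: either the household step already described, or a random draw from a combined list of married and unmarried women. Do not use the unmarried-only list as a stand-alone frame.

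Record marital status and sampling route (list or household) for each WRA, if this is not already done, so that any completed round can be standardised to a common marital mix.

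The cost is a short change to the sampling text, at most two questionnaire items, and slightly more household enumeration in villages that would have used the list. No additional participants are needed.

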1. **Test–Treat-Track until resolution**: Systematic annual hemoglobin screening will be conducted for all beneficiaries across the six study sites. This screening will serve as the primary entry point for identifying individuals with anemia. Individuals diagnosed with anemia will receive appropriate treatment and be monitored until resolution. Mechanisms will be in place to track both nutritional and non-nutritional causes of anemia, such as sickle cell disease and thalassemia. The strategy will primarily focus on four high-burden groups children 6–59 months, adolescent girls, pregnant women, and women of reproductive age. Adolescents’ boys and younger children (5–9 years) will also be included in the strategy. Regular quarterly follow-ups by frontline workers will help ensure treatment compliance, early relapse detection, and sustained recovery.2. **Prophylactic iron and folic acid supplementation:** In parallel with screening, prophylactic IFA supplementation will be implemented to mitigate the risk of anemia across populations. ASHAs and Anganwadi workers will maintain updated beneficiary line lists and ensure the distribution of tablets or syrups in accordance with program guidelines. Counseling and follow-up will be emphasized to enhance adherence, address common barriers such as side effects, and ensure continuity of prophylaxis.3. **Anemia relevant health interventions:** To comprehensively address anemia, the intervention package will integrate maternal, child health, and infection-control practices. This includes promotion of delayed cord clamping at birth, iron supplementation for low-birth-weight infants, and routine deworming. Water, Sanitation, and Hygiene (WaSH) behaviors will be promoted as preventive measures. Additionally, individuals diagnosed with acute or chronic infections such as malaria, tuberculosis, HIV, or hepatitis will also undergo anemia screening and receive appropriate management, thus linking infectious disease control with anemia reduction.4. **Fortified rice through Public Distribution Systems:** Nutrient security will be strengthened by leveraging government-supported food distribution programs. Fortified rice is already being distributed through the Public Distribution System (PDS), Integrated Child Development Scheme (ICDS), and Pradhan Mantri Poshan Shakti Nirman (PM-POSHAN) (mid-day meals) but through the study there will be efforts to generate community awareness and sensitization campaigns to promote acceptance and regular consumption of fortified rice. Monitoring will be conducted using official distribution records and household surveys to assess uptake and effectiveness in addressing dietary iron gaps.5. **Dietary diversification and promotion of iron-rich foods:** Dietary modification is an essential pillar for long-term anemia prevention. The intervention will promote consumption of iron, folate, and vitamin B12-rich foods, including millets and other traditional staples. Beneficiaries will be counseled at Village Health and Nutrition Days, Ayushman Arogya Mandirs, Self-Help Groups, and Anganwadi Centres. Practical demonstrations such as recipe sessions and use of dietary diversity checklists will reinforce key messages. Schools will serve as a critical platform, incorporating nutrition education into the curriculum, training student health ambassadors, and organizing activities under the “Eat Right” campaign. Program menus under PM-POSHAN and ICDS will also be reviewed to align with micronutrient standards. Communication strategies will employ Information, Education, and Communication (IEC) materials, Short Message Service, social media, and Ayush Ahaar campaigns to reinforce consistent dietary practices.6. **Behaviour change communication through Jan Andolan:** Finally, community engagement through Jan Andolan will ensure sustainability and collective responsibility for anemia control. This approach will emphasize advocacy, capacity building, and partnerships with schools, self-help groups, and local organizations. Social mobilization efforts will highlight the importance of annual screening, adherence to IFA supplementation, acceptance of fortified foods, and inclusion of diverse diets in daily meals. By positioning anemia reduction as a community priority, the intervention aims to build momentum toward a sustained, population-level movement.

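### Listed groups are sampled from health-worker line lists that the intervention will extend after baseline, so the trends can mix true change with change in who can be sampled

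*Protocol article*

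**What the plan says.** All of this is in the Protocol article.

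- **Frame.** Under Sampling strategy, the universe is the whole district. Lists of children, pregnant women, adolescent girls and, where available, unmarried women of reproductive age "will be collected from ASHA/ANMs/AWWs", and respondents in these groups are drawn at random from them.
- **Frame change.** The same section concedes that the "line listing will not have 100% coverage, but as a part of implementation research study, this aspect will be strengthened". The timing is given as well: "this aspect will be strengthened as interventions are rolled out".
- **Who keeps the lists.** In the intervention package, under the iron and folic acid pillar, "ASHAs and Anganwadi workers will maintain updated beneficiary line lists". The same workers distribute the supplements.
- **Groups without a list.** These are sought in the next one or two households beside a household found through the list. The groups named include "WRA & adolescent girls (incase CHWs do not have readily available list for WRA").
- **Constancy.** "The method of sampling would be the same in each of the five survey rounds".
- **Use of the rounds.** Study phases puts the baselines at months 3 and 9, implementation at months 10 to 39, and later surveys at months 18, 30 and 36. Study design and setting plans an interrupted time series. The objectives closing the Introduction are prevalence of 20% or less and population-based coverage of at least 80%.

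**The concern.** An interrupted time series compares rounds on the understanding that each represents the same population. Here the frame is incomplete at baseline by the plan's own account, and it is widened by the intervention over the same months in which the effect is to be measured. A step or slope after month 9 could then come from the programme, from newly listed people entering the frame, or from both.

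The statement about a constant method fixes the procedure, not the list to which it is applied. For women of reproductive age and adolescent girls, both primary-outcome groups, even the procedure is conditional: the list where one exists, a neighbouring household where it does not. A village that gains a usable list between rounds would change mode.

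At stake are the primary prevalence trend and the coverage objective. A larger sample or cluster adjustment would not remove such a bias. If list status is not recorded in the field, no later analysis can recover it.

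**Working it through.** **Inputs from the article:** baseline prevalence 40–60%; end-line prevalence 20% with 30% relative precision; design effect 1.45; non-response 40%, 30% and 20%; sample sizes 400, 350 and 300 per group and round.

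**Assumed, because the article gives no figure:** list coverage c0 at baseline and c1 later; prevalence pL in people listed at baseline and pU in people not listed; gap Δ = pU − pL; true overall prevalence constant at 50%.

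**Step 1: a yardstick from the plan.** The absolute precision is 0.30 × 20 = 6 points. The formula gives 1.96² × 0.20 × 0.80 / 0.06² = 170.7, and × 1.45 = 247.6 responders. Dividing by 0.6, 0.7 and 0.8 gives 412.6, 353.7 and 309.5, against the stated 400, 350 and 300. The stated figures are slightly low and look rounded down: 400 × 0.6 = 240 responders gives 30.5% relative precision. So ±6 points is a fair yardstick. Nothing below depends on it.

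**Step 2: prevalence with no true change.** A list-only sample expects pL at baseline. Later it expects (c0·pL + (c1 − c0)·pU) / c1. The difference is Δ × (c1 − c0) / c1.

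For c0 = 0.70, c1 = 0.95 and Δ = 10 points:
- pL = 50 − 0.30 × 10 = 47.0 and pU = 57.0
- later round = (0.70 × 47.0 + 0.25 × 57.0) / 0.95 = 47.15 / 0.95 = 49.6
- spurious change = +2.6 points

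| List coverage | Δ = −10 | Δ = 0 | Δ = +10 | Δ = +20 |
|---|---|---|---|---|
| 60% to 95% | −3.7 | 0 | +3.7 | +7.4 |
| 70% to 95% | −2.6 | 0 | +2.6 | +5.3 |
| 80% to 95% | −1.6 | 0 | +1.6 | +3.2 |
| 90% to 95% | −0.5 | 0 | +0.5 | +1.1 |

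**Step 3: a coverage indicator with no true change.** Assume 70% coverage in listed and 35% in unlisted people. With 70% list coverage, baseline reads 70%, while population coverage is 0.70 × 70 + 0.30 × 35 = 59.5%, an overstatement of 10.5 points. With 95% list coverage, the later round reads (0.70 × 70 + 0.25 × 35) / 0.95 = 60.8%, an apparent fall of 9.2 points. Starting from 60%, 80% and 90% list coverage, the apparent falls are 12.9, 5.5 and 1.8 points.

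**Step 4: the end-line level alone.** In the 70% to 95% case with Δ = +10, the later round differs from the truth by 49.6 − 50 = −0.4 points. The trend is affected far more than the level, provided the lists do become nearly complete.

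**Step 5: does the household step cure this?** No. It serves groups for which no list is ready and does not add unlisted members of groups that have one. Its households are also found from listed beneficiaries, so it too moves with the list.

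**The case against.** The best defence has four parts.

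- **No evidence of a gap.** The article has no data showing that unlisted people differ. If they do not, the artefact is zero. This stands, and it is why the point is conditional. A gap is plausible, since the workers who keep the lists also deliver the services, but it is not shown.
- **Conservative direction and modest size.** If unlisted people are more anemic and less served, the improvement is understated. The hoped-for fall is 20 to 40 points (from 40–60% to 20%), and the end-line target is a level that is little affected once lists are nearly complete. This also stands, under that sign of the gap. The opposite sign would flatter the programme, and the article does not settle which applies.
- **One procedure is fixed for all rounds.** A mode switch is permitted by the conditional rule but is not planned, and nothing says that new lists will be made for women of reproductive age. This is correct: the fault is that the rule allows the change.
- **A journal article leaves field detail to the full protocol.** That is fair for weights and field forms. The selection rule and the expected change in the frame, however, are stated here, and they create the problem.

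Two stronger readings are tempting and should not be drawn. A reader might infer that better lists bring earlier pregnancy registration and so shift the trimester mix behind an outcome defined for "pregnant women (all trimesters"). No section makes earlier registration an aim or an expected effect. A reader might also equate the baseline frame with people already served. The lists are of beneficiaries, list upkeep and supplement distribution are separate tasks, and the Introduction names variable supplement coverage and adherence as a known problem, so listed people can be unserved.

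**Conclusion.** The point holds in conditional form. The frame is incomplete at baseline, is widened by the intervention afterwards, and feeds a trend evaluation for the whole district. If listed and unlisted people differ, the prevalence and coverage trends mix true change with frame change. In addition, the rule for two primary-outcome groups leaves the selection mode free to change between rounds, despite the statement that the method is constant.

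Direction and size cannot be fixed from the article. With list coverage rising from 70% to 95% and a 10-point gap, the artefact is about 2.6 points. For gaps up to 10 points, and baseline list coverage of 60% to 90% rising to 95%, it runs from 0 to about 4 points either way. Coverage measured among listed people overstates population coverage if unlisted people are less served. These results rest on assumed list coverage and gaps. They do not show that the trends are in fact biased, or that the bias favours the programme.

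**What to change.** 1. Set one selection mode per group for all five rounds, whether or not a list becomes available later.
2. In the adjacent households already visited, enrol eligible children and pregnant women who are not on the list, and record list status for every respondent.
3. Report estimated list completeness by round. Give prevalence and coverage trends by list status, with a sensitivity analysis weighted by list status.
4. State that adjacent households are anchored to listed ones, so that these steps reduce and gauge the bias without removing it. Pockets far from any listed household remain unsampled. Independent household enumeration in every round would be stronger but costlier.

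The cost is slightly more field time, one extra variable, and somewhat larger variance from weighting. The baseline frame cannot be rebuilt afterwards. If the baseline rounds are already done, apply this to the remaining rounds and report the baseline limitation.
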